### Plans to give access to the full protocol, participant-level data, and statistical code {31c}

Only the study investigators will have access to the raw data and hardcopies. De-identified and aggregated data may be obtained from the research team upon reasonable request.

The sponsor institution (HCA) will permit study-related monitoring, audits and/or IRB review and regulatory inspections, providing direct access to source data/document.

## Oversight and monitoring

### Composition of the coordinating centre and trial steering committee {5d}

This clinical trial is supported by HCA’s research department. A Research Executive coordinates organisational support for the trial and manages the research team’s meeting and supports the research team’s overseeing of the trial.

### Composition of the data monitoring committee, its role and reporting structure {21a}

A data monitoring committee (DMC) was not sought for this clinical trial due to the following reasons. First, the trail is open label. Second, the medications used are widely used in both hospital and community, with a well-known risk profile that are minimal and manageable by clinical staff and the caregivers.

### Adverse event reporting and harms {22}

Related adverse events are defined as events where there is a reasonable possibility that the adverse event (AE) may have been caused by participation in the clinical trial. Relatedness may be graded as one of three options: definitely, probably, or possibly.

Any complaints, adverse event, serious adverse event, or incidence must be reported to the Principal Investigator. Follow-up information will be actively sought and submitted as it becomes available. All related AEs will be recorded and filed as a Research Incident Report Form in the patient’s study file.

For all AEs, the study team and the medical director of HCA will be notified to review the incident and discuss changes or improvements to be made to address the complaint. For serious AEs, a report will be submitted to both the IRB and the Health Sciences Authority (HSA).

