### Provisions for post-trial care {30}

As this trial involves patients whose prognoses are between 3 and 7 days, patient death is expected by the end of the trial. However, in the event the patient outlives the prognoses and survives, the patient’s primary nurse and staff will continue to provide standard palliative care to the patient. At this point, medical advice and end-of-life decisions will be made independently from the study. The patient’s survival (whether alive, discharged, or deceased) will be monitored up to day 7 of recruitment. If the patient is still alive after day 7, their data will be removed from the main analysis as they would no longer fall under the inclusion criteria of an imminently dying patient.

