## Assignment of interventions: blinding

### Who will be blinded {17a}

This study was designed as an open-label study and thus there was no blinding between trial participants, care providers or the researchers.

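### The incident record covers only adverse events judged related, the by-arm comparison names three toxicities, and day-7 survival is used only to remove patients, so harms that resemble dying enter no stated comparison

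*Protocol article*

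**What the plan says.** All references are to the protocol article.

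- **Adverse event reporting and harms {22}.** Notification is broad: "Any complaints, adverse event, serious adverse event, or incidence must be reported to the Principal Investigator". The study team and the medical director review all events, and serious events also go to the IRB and HSA. The filing rule is narrower: "All related AEs will be recorded and filed as a Research Incident Report Form". On grading: "Relatedness may be graded as one of three options: definitely, probably, or possibly". The section does not name who judges relatedness.
- **Plans for assessment and collection of outcomes {18a}, CTCAE paragraph.** Over-sedation and three extrapyramidal terms are named as possible side effects. To track these, the study physician rates observed events at 24, 48 and 72 h. Relatedness is not a condition.
- **Statistical methods {20a}.** The toxicities to be compared between groups are akathisia, extrapyramidal disorder and spasticity.
- **Who will be blinded {17a}.** "there was no blinding between trial participants, care providers or the researchers".
- **Provisions for post-trial care {30}.** "patient death is expected by the end of the trial", and survival "will be monitored up to day 7 of recruitment". Patients alive after day 7 are then taken out of the main analysis. The CTCAE paragraph of {18a} applies the same exclusion to the per-protocol analysis instead.

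**The concern.** In a population this close to death, a drug-related event can look the same as the illness running its course. Aspiration, a fall, a seizure or an early death can each be explained either way. If the explanation decides whether an incident record is made, and the arm is known to everyone who might give it, the incident record depends on opinion as well as on events. The usual protection is to record everything and compare all-cause counts by arm, so that randomisation does the attribution.

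Death is the clearest case, because judging deaths one by one tells little when nearly all are expected. Only a comparison between arms is informative. The data for it are collected, but the one use stated for them is as an exclusion rule. At stake are the credibility of the safety conclusion and the reader's ability to see whether survival differed between arms. Survival also decides who is still there for the 48 h and 72 h MDAS ratings.

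**Working it through.** The plan gives no figure to reproduce on this point. The check is mainly a comparison of sections, followed by three short calculations on stated assumptions.

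**1. Three scopes for harms**

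| Section | Events covered | Relatedness filter | By-arm comparison stated |
|---|---|---|---|
| {22}, notification and review | all | no | no |
| {22}, filed incident form | related only | yes | no |
| {18a}, CTCAE rating | observed events, framed around over-sedation and extrapyramidal effects | no | through {20a} only |
| {20a}, comparison | akathisia, extrapyramidal disorder, spasticity | no | yes |

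Take an aspiration that is put down to dying. It is notified to the Principal Investigator and reviewed, and reported onward if serious. It has no relatedness grade and needs no incident form. It may or may not be rated under CTCAE, depending on how narrowly {18a} is read. On either reading it is outside the three terms in {20a}. Over-sedation is named in {18a} but is also missing from {20a}.

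**2. What a related-only filter does to incident-form counts (illustration)**

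Expected forms per arm = n × event rate × probability of being judged related. The article states 80 patients at 1:1, so n = 40. Assume a true event rate of 20% in both arms: 40 × 0.20 = 8 events each.

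- 60% judged related in both arms: 8 × 0.6 = 4.8 v 4.8, ratio 1.
- 60% v 30%: 8 × 0.6 = 4.8 v 8 × 0.3 = 2.4, ratio 2.
- None judged related: 0 v 0.

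With equal true rates, the ratio of forms equals the ratio of attribution probabilities, whatever the event rate. The percentages are assumptions. The sum concerns incident forms, not the CTCAE outcome.

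**3. What the day-7 exclusion does (illustration)**

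The article gives no death rate. Suppose 50% v 70% have died by day 7.

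- Removed as survivors: 40 × 0.50 = 20 v 40 × 0.30 = 12.
- Retained: 20 v 28.

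A 20-point survival difference would change the analysis set by 8 patients between arms. Because survivors have been removed, comparing day-7 survival status within the retained set would not show it.

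**4. What a survival comparison in all randomised patients could show**

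Time to death, Schoenfeld formula, two-sided alpha 0.05, power 0.80, 1:1 allocation: detectable HR = exp[(1.96 + 0.842)/√(0.25 × deaths)].

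- 80 deaths: exp(2.802/4.472) = 1.87. Power for HR 1.5 is 44%.
- 56 deaths: exp(2.802/3.742) = 2.11. Power for HR 1.5 is 33%.

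Precision, with SE(log HR) ≈ 2/√deaths: for 80 deaths the SE is 0.224, so the 95% interval is the estimate divided and multiplied by exp(1.96 × 0.224) = 1.55.

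Proportion dead by day 7, 40 per arm, normal approximation: power = Φ{[d − 1.96√(2p̄(1−p̄)/n)] / √[(p₁(1−p₁) + p₂(1−p₂))/n]}.

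| Assumed dead, one arm | Difference detectable with 80% power | Power for 10 points | Power for 20 points |
|---|---|---|---|
| 30% | 31 points | 15% | 45% |
| 50% | 30 points | 14% | 45% |
| 70% | 24 points | 18% | 61% |

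For the example in step 3: [0.20 − 1.96 × 0.1095]/0.1072 = −0.14, giving a power of about 45%.

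**The case against.** The strongest reply is that the related-only sentence governs one administrative form. The toxicity outcome comes from the CTCAE ratings, which carry no relatedness condition, and no section says that the analysis draws on incident forms. Every event reaches the Principal Investigator, the study team and the medical director, and every serious event reaches the IRB and HSA. Monthly audits cover adverse events. RASS runs down to unarousable, is charted every 6 h and is compared by arm. The relatedness scale may simply grade events already classed as related, in which case it needs no lower grade. Finally, this is a journal article: a mortality table may sit in an analysis plan or full protocol that is not shown.

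Most of this stands, and it rules out several stronger readings that a reader might infer:

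- That only related events are recorded anywhere. The CTCAE rating contradicts this.
- That harm resembling dying cannot be detected. RASS picks up deep sedation, and deaths could be tabulated from the status collected.
- That survival will never be compared. The article states no comparison, which is all that can be said.
- That the assessor of relatedness is known to be unblinded. No assessor is named; it is an inference from {17a}, though a strong one.
- That reporting of expected deaths as serious events is mishandled. An article commonly leaves that to the full protocol.

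The reply does not deal with two things the article does state. Notification and review are not said to yield a record that can be compared by arm, and the one stated comparison is limited to three terms that leave out over-sedation. The use of day-7 survival to remove patients is a written rule, so an unseen document cannot excuse it as a mere omission.

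**Conclusion.** The point holds in a limited form. Sections {22}, {18a} and {20a} give different scopes for harms, and the only filing rule is selective by judged relatedness in an open-label trial of dying patients. Harms outside the three listed toxicities may be attributed to the illness and enter no stated by-arm comparison. Separately, day-7 survival is an outcome that either drug could affect, and using it only to exclude patients could mask a difference between arms.

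The size of any bias cannot be derived from the article. The twofold ratio of forms and the 20 v 12 removals rest on assumed rates and show direction and mechanism only. The gain from the remedy is also bounded. With 80 patients, a survival comparison would reliably show only large effects (hazard ratio about 1.9 if all die, or 24 to 31 percentage points for assumed death proportions of 30% to 70%). It would make moderate differences visible with an interval, without settling them. The change is worth making because it is cheap, not because the trial would otherwise have no safety data.

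**What to change.** - **{22} and {18a}:** reconcile the two so that every adverse event is recorded whatever its judged cause. Make relatedness a separate field that includes a not-related option, and state who completes it.
- **{20a}:** add a summary of all-cause adverse events by randomised arm, which also brings in over-sedation, alongside the three terms already listed.
- **{30} and {20a}:** report deaths and time to death to day 7 by randomised arm in all randomised patients, for example as Kaplan-Meier curves with a hazard ratio and 95% interval. Label this a descriptive safety result, not a powered test. Patients alive after day 7 must stay in this summary, whatever is decided about the exclusion elsewhere.

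The cost is somewhat more form-filling for events judged unrelated, and one extra table or curve from data already collected. No extra visits or staff are needed.

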### Frequency and plans for auditing trial conduct {23}

Audits from trial conduct will be done monthly by the study team. An audit will include a review of subject eligibility, informed consent process, protocol compliance, disease outcome, adverse events and toxicity, data quality, regulatory documentation, and investigational product records.

### Plans for communicating important protocol amendments to relevant parties (e.g. trial participants, ethical committees) {25}

Only the study investigators would be allowed to propose modifications to the trial protocols. In the event that a modification of the protocols must be enacted, trials and recruitment will be stopped. Any modifications to the protocols planned must first be submitted to the IRB for review and approval, followed by a submission to HSA. Once approved, the protocol may be modified per the proposal and the participants shall be notified.

### Dissemination plans {31a}

Findings from this clinical trial should be analysed and published in a peer-reviewed journal at the end of the study. The study will credit all investigators listed in this protocol as authors. Acknowledgement may be given to any members who have contributed to the conduct of the trials and the writing of the report.

## Discussion

To compare the efficacy of two pharmacological treatments of terminal delirium in dying patients on hospice care, a prospective, randomised, open-label trial will be conducted at home setting. The two groups of patients will be receiving OT haloperidol and olanzapine respectively.

Findings from this study will contribute to scarce evidence of anti-psychotics/ neuroleptics use in the treatment of terminal delirium for patients receiving home hospice care. It would inform future practice on appropriate medication to treat delirium during the dying phase. With optimised care, the end-of-life experience of patients and their caregivers will be improved.

Some facts were discussed during the study design. First, a blinded design will not be possible or necessary. Due to limited clinical evidence of pharmacological treatment of terminal delirium in the home environment, the additional blinding procedures are hazardous and not providing any added value. Second, proxy consent has been chosen instead of advance consent. To approach patients before the onset of terminal delirium is neither feasible nor appropriate considering the potential unnecessary stress caused to the vulnerable group of patients in their terminal phase.

## Trial status

The study was reviewed and approved by the Agency for Integrated Care Institutional Review Board (AIC-IRB). Clinical Trial Authorisation is pending from the Health Sciences Authority Singapore (HSA). Recruitment is projected to start in August 2021.

## Abbreviations

OT: Oral transmucosal
DSM-V: Diagnostic and Statistical Manual of Mental Disorders – Fifth Edition
IRB: Institutional Review Board
HSA: Health Sciences Authority
MDAS: The Memorial Delirium Assessment Scale
RASS-PAL: The Richmond Agitation-Sedation Scale modified for palliative care
NCI CTCAE: National Cancer Institute Common Terminology Criteria for Adverse Events
SC: Subcutaneous
ANOVA: Analysis of variance
